## Abstract

**Background:**

Currently there are campaigns to raise the awareness of the need to practice physical exercise with several objectives, mainly as a preventive measure. The Pilates method is a form of therapeutic exercise for maintaining and improving health. However, despite being popular, there is still no scientific evidence on the standardization and progression of the method. Therefore, the purpose of this study was to develop a protocol to monitor the progression of daily Pilates loads between the basic, intermediate, and advanced levels, as well as to analyze the effects of the method on psychometric, cardiorespiratory, and autonomic measures.

**Methods/design:**

In total, 54 healthy men underwent 36 sessions of Pilates mat work. Before each training session, cardiorespiratory measures, pain (visual analogue scale), and a psychometric questionnaire were collected. Heart rate (HR), subjective perception of effort (SPE), and RR intervals were measured during the sessions and used later in the analysis of the progression of training load by monitoring the internal training load and heart rate variability. At the end of the sessions, cardiorespiratory measures, the visual analogue scale, and the psychometric questionnaire were measured again. After 15 min of rest, the final HR measurement was made and the participants noted the effort on the SPE scale. The psychometric, cardiorespiratory, and autonomic measures were evaluated before and after each of the 36 training sessions.

**Discussion:**

This is a parallel randomized clinical trial of standardized Pilates training, with the aim of estimating training loads and measuring the efficacy of Pilates through clinical, cardiorespiratory, and autonomic outcomes. The protocol can easily be reproduced and could be used to support professionals in prescribing the method.

**Trial registration:**

ClinicalTrials.gov, NCT03232866. Registered on 28 July 2017.

**Electronic supplementary material:**

The online version of this article (10.1186/s13063-019-3684-x) contains supplementary material, which is available to authorized users.

## Background

The Pilates method is an alternative therapeutic exercise for protecting against risk factors and promoting health [1]. However, only one literature review investigates the Pilates method [2]. The methodological quality is low, which demonstrates the lack of standardization of the method and the load progression as a form of physical training [2]. Thus, for the safe prescription of resistance exercises, such as the Pilates method, physiological variables, such as heart rate (HR) [3] and cardiac autonomic modulation [4, 5], and subjective variables, such as subjective perception of effort (SPE) [6], need to be monitored.

Thus, there is a need to identify simple and low-cost methods for controlling the intensity of exercises, due to the adaptations made by the psychobiological system through training, such as improvements in exercise tolerance and physical performance [7]. It would be beneficial to use SPE together with HR to quantify the training intensity of the Pilates method, as well as to use cardiac autonomic modulation to assess the oscillations of the cardiac autonomic nervous system during training, since heart rate variability (HRV) is considered an early and sensitive indicator of health impairment. HRV indicates the adaptability of cardiac autonomic control to a stimulus [8, 9].

Although the Pilates method is becoming more widespread and has shown promising clinical and functional outcomes in rehabilitation [10, 11], quality clinical trials are needed to analyze the intensity of the training. The results of such trials may offer greater support for tools that can assist in the prescription and load progression of Pilates practice, while demonstrating the effects of the method on the cardiovascular system and autonomic control.

Therefore, the objective of this protocol is to monitor the daily load progression from the basic and intermediate levels to the advanced level by measuring HR, SPE, and HRV for 12 weeks, as well as to analyze the effect of the method on psychometric, cardiorespiratory, and autonomic measures. It is hypothesized that the protocol proposed by the study can be prescribed clinically, proving that SPE, HR, and HRV are useful tools for monitoring the progression of Pilates training loads. Furthermore, SPE is expected to have a good correlation with HR and clinical relevance, thus giving practitioners two simple low-cost monitoring tools. In addition, it is hypothesized that the psychometric, cardiorespiratory, and cardiac autonomic modulation measures will have improved after 12 weeks of training.

## Methods/design

### Study design

A parallel randomized clinical trial is being conducted at the Center for Studies and Assistance in Physiotherapy and Rehabilitation of the Universidade Estadual Paulista (FCT/UNESP), Presidente Prudente, São Paulo, Brazil. The trial was registered at ClinicalTrials.gov (NCT03232866) and approved by the research ethics committee of FCT/UNESP (protocol 061942/2017). The study protocol follows the SPIRIT 2013 checklist (Standard Protocol Items: Recommendations for International Trials) [12] (Additional file 3) and TIDieR (Template for Intervention Description and Replication) [13], indicating that information about and the quality of the reports of the interventions are well described [14]. Prior to participation, the volunteers received oral and written instructions and signed a consent form agreeing to participate in the study. All personal data will remain confidential. Note that, although very unlikely, participants who suffer any kind of injury as a result of participation will receive a free medical evaluation and physiotherapy treatment.

Participants were divided into two groups: the Pilates group and the control group. Participants in the Pilates group underwent 12 weeks of Pilates exercises for three times a week, for a total of 36 sessions. Each session lasted for approximately 60 min. During this training period, participants were required to pass through the three levels of the Pilates method: basic, intermediate, and advanced. The control group were asked to maintain their current level of daily activities without taking any type of exercise training. A flowchart for the study and group composition are shown in Fig. 1.

**Fig. 1 Fig1:**
[figure not shown]
Flowchart of the study

### Participants

A total of 54 healthy male volunteers were recruited from the local university (UNESP) through pamphlets, online media, personal invitations, telephone calls, and SMS messages. These procedures were recommended by Treweek et al. [15] as strategies to improve participant recruitment.

The inclusion criteria were: male; 18 to 35 years of age; healthy (self-report); not having practiced Pilates prior to the study; not a smoker or an alcoholic; not presenting with a metabolic, cardiac, or endocrine disorder; with no arrhythmia; not using drugs that influence the autonomic modulation of the heart; and without physical limitations such as musculoskeletal, inflammatory, or neurological diseases that would prevent them from doing Pilates.

Individuals who suffered from a musculoskeletal injury during training, those who attended less than 85% of training sessions, those who failed to progress between the three levels of the Pilates method, those who were unable to respond adequately to subjective scales, and those with errors in the captured RR intervals were excluded from the study. Participants were instructed to maintain their daily dietary routine, to abstain from taking anti-inflammatory medications and analgesics, and not to perform any other type of exercise during the intervention period. These requests were reinforced during the training period and monitored by self-report [16].

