**Fig. 2 Fig2:**
[figure not shown]
Study outline. VAS visual analog scale BP blood pressure, HR heart rate, *f* respiratory rate, SatO_2_ oxygen saturation, SPE subjective perception of effort

At the end of the 36 Pilates training sessions, the final evaluation was carried out. This included cardiorespiratory measures, the psychometric questionnaire, and HRV. The control group underwent only the initial and final evaluations, like the Pilates group.

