The cutoff points for load increments with the HRV indices and SPE were obtained from the receiver operating characteristic curve. The sensitivity, specificity, positive predictive value, and negative predictive value for each level of the Pilates method will also be calculated. The area under the curve will be considered significant when values ≥0.65 are obtained [38]. In addition, a comparison will be made between the receiver operating characteristic curves of each HRV index to detect the most representative for determining the internal training load of the Pilates method.

The statistical analysis will be carried out with the *Statistical Package for the Social Sciences*, version 15.0 (SPSS Inc., Chicago, IL) and *MedCalc Software bvba*, version 14.10.2 (Oostende, Belgium). All data will be entered into the software twice. All participants included in the initial assessment will be considered under the intention-to-treat approach in which the worst outcome obtained by the study group will be selected to ensure the power of the data analysis.

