## Discussion

Previous systematic reviews have found a beneficial effect of Pilates on risk factors for various diseases, as well as positive responses in outcomes such as strength, flexibility, low back pain, and quality of life, among others [2, 39, 40]. However, the low methodological quality of previous studies and the lack of load monitoring of the exercises do not allow definitive conclusions to be drawn about the effect of the Pilates method. Moreover, there have been few studies investigating the effects of Pilates on the cardiac autonomic nervous system.

Methodological characteristics commonly found in studies published in the literature include lack of concealed allocation, no intention-to-treat analysis, unblinded assessors, lack of standardization of training on biological principles, and low familiarization of participants with the method. This study is a parallel randomized clinical trial to measure the effectiveness of the Pilates method on the cardiac autonomic nervous system and, mainly, to analyze methods of monitoring training loads.

The best measures for quantifying the internal load are SPE and HR, because they are cheap and simple to use. They can be measured by any healthcare professional. HRV is also important as an early and sensitive indicator of health impairment; however, correct analytical use of this tool requires detailed knowledge.

The training protocol described in this study was based on the most recent literature. A strength of the study is the parallel randomized clinical trial design with an intention-to-treat analysis. Moreover, the protocol is easy to replicate. However, a limitation is the inability to blind participants to their allocation.

This study may contribute by providing further information on the real autonomic benefits provided by this type of physical exercise and can be used to guide practitioners in prescribing the method, as well as offering more support to practitioners.

Note that this study uses the checklist of items for protocol studies to minimize bias. It was prospectively registered. The outcomes will be disseminated through publications in scientific journals and presentations at area congresses.

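### Exclusions after randomization that only the Pilates arm can meet are not reconciled with the claimed intention-to-treat analysis

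*Protocol article*

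**What the plan says.** The Participants section lists, after the inclusion criteria, men who leave the study. Two of the reasons concern attendance and progression: "those who attended less than 85% of training sessions, those who failed to progress between the three levels of the Pilates method". The list also names men injured while training, men unable to answer the subjective scales adequately, and "those with errors in the captured RR intervals were excluded from the study".

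The Statistical analysis section states that "All participants included in the initial assessment will be considered under the intention-to-treat approach", and adds that men are to be given the worst result seen in the study group. The Discussion repeats the claim: "A strength of the study is the parallel randomized clinical trial design with an intention-to-treat analysis". It also lists the lack of such an analysis among the weaknesses of earlier studies.

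On the two arms, Study design says of the Pilates arm: "Participants in the Pilates group underwent 12 weeks of Pilates exercises for three times a week, for a total of 36 sessions". Of the other arm it says: "The control group were asked to maintain their current level of daily activities without taking any type of exercise training". The text under Fig. 2 adds: "The control group underwent only the initial and final evaluations, like the Pilates group". The Randomization section places baseline collection before randomization.

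**The concern.** Training starts after randomization, so injury in training, low attendance and failure to progress are all post-randomization events. A control man has no sessions to miss, no levels to pass and no training in which to be injured. Three of the five exclusion reasons can therefore remove men from one arm only.

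Two things are at stake.

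- **Between-group comparisons** (HRV, cardiorespiratory and psychometric measures). If the excluded men are dropped, adherent and uninjured Pilates men are set against all controls, and randomization no longer protects the comparison.
- **Load monitoring and ROC cut-offs.** These come from the Pilates arm alone. If men who did not adhere or progress are dropped, the results describe only those for whom the progression worked, although the article offers them as a guide to prescription in general.

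**Working it through.** **1. The two rules side by side.** 85% of 36 sessions is 0.85 × 36 = 30.6, so a Pilates man who attends 30 or fewer meets the attendance criterion. Under Participants he is out of the study. Under Statistical analysis he is in, because he had an initial assessment. No sentence says which rule prevails or how they combine.

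**2. The plan's own figure.** Inputs from Sample size calculation: difference 19.02 ms, SD 23.94 ms, two-sided 5%, power 80%. Then n per group = 2 × [23.94 × (1.960 + 0.842) / 19.02]² = 24.9, so 25, as stated. The plan then allows 10% for withdrawals and takes 27 per group. These values set the scale below.

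**3. If the excluded men are dropped.** Assumptions not in the document: no true effect; a fraction p of Pilates men is removed; proneness to removal correlates ρ with a poorer final rMSSD; no control is removed. The Pilates mean shifts upward by ρ × φ(z_p) / (1 − p) standard deviations, where φ(z_p) is 0.1755 at p = 0.10 and 0.2800 at p = 0.20. The chance of a significant result favouring Pilates comes from the noncentral t distribution, with 24 v 27 men (p = 0.10) or 22 v 27 (p = 0.20).

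| p | ρ | shift (SD) | shift (ms) | share of 19.02 ms | false-benefit rate |
|---|---|---|---|---|---|
| 0.10 | 0.3 | 0.0585 | 1.40 | 7% | 4.0% |
| 0.10 | 0.5 | 0.0975 | 2.33 | 12% | 5.3% |
| 0.20 | 0.3 | 0.105 | 2.51 | 13% | 5.5% |
| 0.20 | 0.5 | 0.175 | 4.19 | 22% | 8.6% |

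The nominal rate is 2.5%. A simulation that drops the 2 to 7 most removal-prone of 27 Pilates men gives 1.0 to 5.0 ms and a two-sided type I error of 5.2% to 11.0%, consistent in direction and order.

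**4. If the worst-outcome clause is applied to these men instead.** The setting is the same, with 3 or 5 of 27 Pilates men given the lowest value among the retained Pilates men. That is my reading of the clause, which does not define the study group. By simulation:

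| men affected | ρ | shift (ms) | false-benefit rate |
|---|---|---|---|
| 3 | 0.3 | −3.6 | 0.7% |
| 3 | 0.5 | −2.5 | 1.2% |
| 5 | 0.3 | −6.0 | 0.4% |
| 5 | 0.5 | −4.2 | 0.8% |

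The sign of the bias thus depends on which passage is followed.

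**5. Power.** Loss of men is the lesser problem. The t-based power is 0.817 with 27 v 27, and 0.793 or 0.773 if 3 or 5 men are dropped from the Pilates arm only.

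**The case against.** The best defence is that the two passages can be read together: a man who meets a criterion stops taking part, stays in the analysis and receives the worst outcome. That clause is needed only for men without a usable final value, so the plan does foresee men leaving. This stands to the extent that a reader should not infer that the rules are flatly incompatible, or that the trial is bound to be biased towards Pilates. It does not remove the problem: Participants says exclusion from the study, nothing connects the passages, and the combined reading brings a bias of its own.

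Other points on that side:

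- **Number affected.** Trial status reports 54 randomized, with all participants attending. Removals may be few or none. This stands, and it limits the harm but does not settle which rule governs. The 10% end matches the plan's withdrawal allowance; the 20% end doubles it.
- **RR-interval errors.** One might infer that these also remove Pilates men much more often, since they are recorded at 36 sessions as well as at the two evaluations. The text does not say that one faulty session removes a man, and Secondary outcomes already screens recordings series by series (more than 95% sinus beats). I therefore do not rest the point on this criterion.
- **Primary outcome.** One might infer that excluding non-progressors selects on the primary result itself. Passing the three exercise levels is related to internal load measured by SPE, HR and HRV, but is not the same thing. What holds is restricted applicability. The loss of randomized comparability concerns the between-group comparisons, not load monitoring.

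**Conclusion.** The point holds. The article states an exclusion rule that acts after randomization in one arm and an intention-to-treat claim, and does not reconcile them. That conclusion needs no assumption. Its size does: followed as written, the exclusions would bias rMSSD by +1.4 to +4.2 ms with a false-benefit rate of 4.0–8.6%. Worst-outcome imputation would instead give about −2.5 to −6.0 ms and 0.4–1.2%. Both ranges rest on assumed removal of about 10–20% of Pilates men and a correlation of 0.3–0.5; the document gives neither. A claim that the plan inflates the Pilates effect holds under one reading only. Under the exclusions, the load and ROC results would apply only to men who adhered and progressed.

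**What to change.** Reconcile Participants with Statistical analysis before the data are analysed:

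- State that meeting one of the listed criteria does not remove a man from the analysis.
- Analyse every randomized man in his allocated arm, using all available final evaluations, and handle values that were not obtained as missing.
- For load monitoring and the ROC analyses, use all sessions delivered to all Pilates men.
- Apply the series-level rule in Secondary outcomes to unusable RR data, so that a bad recording costs that series and not the man.
- Keep attendance of at least 85% with progression through the three levels only to define a labelled per-protocol sensitivity set.

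Whether these criteria also serve to stop training is for the investigators.

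The cost is a wording change and one extra sensitivity analysis, and possibly a smaller estimated effect. Trial status says data were collected in June 2019, so final evaluations that were not done may no longer be obtainable; hence the reliance on available evaluations.

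### Three training-linked exclusions after randomisation, which as worded only the Pilates arm can meet, contradict the promised intention-to-treat analysis, and the protocol does not say which rule prevails

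*Protocol article*

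**What the plan says.** The Participants section of the protocol article lists men who are removed after entry. Three of the criteria are tied to training:

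- injury: "Individuals who suffered from a musculoskeletal injury during training";
- attendance: "those who attended less than 85% of training sessions";
- progression: "those who failed to progress between the three levels of the Pilates method".

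Two further criteria, inadequate answers on the subjective scales and faulty heart-beat recordings, are not tied to training. The list ends with "those with errors in the captured RR intervals were excluded from the study", so the stated consequence for all five is removal from the study, not from one analysis set.

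The Statistical analysis section says: "All participants included in the initial assessment will be considered under the intention-to-treat approach". The same sentence adds that the worst outcome obtained by the study group will be taken, without saying for which men. The Discussion repeats the claim: "A strength of the study is the parallel randomized clinical trial design with an intention-to-treat analysis". It also lists the lack of such an analysis among the weaknesses of earlier studies.

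On what each arm does, Study design says: "Participants in the Pilates group underwent 12 weeks of Pilates exercises for three times a week, for a total of 36 sessions". Controls were asked to do no exercise training. The text after Fig. 2 says: "The control group underwent only the initial and final evaluations, like the Pilates group". The Randomization section places baseline measurement before allocation, so attendance, progression and training injury become known only after it.

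**The concern.** A man cannot be both excluded from the study and included in an analysis of everyone initially assessed. The conflict also falls unevenly. A control has no sessions to miss and no levels to climb, so the attendance and progression rules cannot touch him. As worded, neither can a rule about injury during training.

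The comparison at stake is the between-group one, by unpaired t test or Mann–Whitney test, of the autonomic, cardiorespiratory and psychometric measures. It is the only randomised evidence in the trial, and rMSSD, the index that sized the trial, is among these measures. Neither test protects against selection after randomisation in one arm. Attendance plausibly goes with motivation, fatigue and health, so the men removed need not resemble those who stay.

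**Working it through.** **The plan's own figure.** The Sample size calculation section uses a difference of 19.02 ms, an SD of 23.94 ms, two-sided 5% and 80% power. The normal formula 2 × [SD × (1.960 + 0.842) / difference]² gives 24.87, so 25 per group, as stated. The 10% allowance gives 25 × 1.10 = 27.5; the plan uses 27 per group, 54 in all. The stated size is reproduced to within rounding and is not in dispute.

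**The attendance threshold.** 0.85 × 36 = 30.6, so a man needs 31 sessions, and six misses exclude him.

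**How many men might fall below it.** The article gives no attendance counts. Assume that each session is attended independently with probability p. The excluded fraction f is then the binomial probability of 30 or fewer out of 36:

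| p (assumed) | f | expected of 27 | chance of losing 3 or more (fewer than 25 left) |
|---|---|---|---|
| 0.95 | 0.8% | 0.2 | 0.1% |
| 0.92 | 6.4% | 1.7 | 25% |
| 0.90 | 14.5% | 3.9 | 77% |
| 0.85 | 45.9% | 12.4 | above 99.9% |

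The curve is steep, so no single row should be read as a forecast. The last row puts mean attendance exactly at the cut-off.

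**Branch A: the exclusions prevail.** If excluded men's final rMSSD lies d below that of the men kept, the mean of the men kept exceeds the whole-arm mean by f × d. With d = 0.5 SD (assumed), which is 0.5 × 23.94 = 11.97 ms:

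- f = 14.5%: 0.145 × 11.97 = 1.7 ms, or 0.07 SD, which is 1.7 / 19.02 = 9% of the target difference;
- f = 45.9%: 0.459 × 11.97 = 5.5 ms, or 0.23 SD.

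A separate simulation had no true effect, 10% to 30% of Pilates men excluded on adherence (24, 22 or 19 of 27 kept) and 20,000 runs per case:

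| adherence–outcome correlation (assumed) | bias towards Pilates | type I error |
|---|---|---|
| 0 | none | about 5% |
| 0.3 | 1.5 to 3.4 ms | 5.8% to 7.5% |
| 0.5 | 2.5 to 5.7 ms | 6.7% to 12.8% |

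Loss of power is modest. Against 27 controls, t-test power is 79.3%, 77.3% or 73.7% with 24, 22 or 19 Pilates men, compared with 81.7% at 27 v 27.

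**Branch B: intention to treat prevails.** Excluded men stay in, but if they are not measured they may be assigned the worst outcome. If that value lies k SD below what they would have shown, the Pilates mean falls by f × k × 23.94 ms. At f = 14.5% this is 0.145 × 23.94 = 3.5 ms for each SD. Controls have no such men to impute, so the shift is against Pilates. The article gives nothing from which to fix k.

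The two branches can pull in opposite directions, and the text does not choose between them.

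**The case against.** A reader might infer that the randomised comparison definitely becomes adherent Pilates men against all controls. The documents do not support that. The Statistical analysis section is the natural place for the rule on who is analysed, and it covers everyone initially assessed. On that reading no one is deleted, and the likely bias is against Pilates. Nor is the control arm untouched: controls can still be excluded for faulty heart-beat recordings or inadequate scale answers, though not for attendance or progression. If injury during training means during the training period, an injured control could be caught too.

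A reader might also infer that many men have been excluded. Trial status reports 54 randomised and all participants attending their groups, which suggests few exclusions, although it gives no attendance counts and the flowchart is not shown. Attendance, independence between sessions and the 0.5 SD deficit are all assumptions.

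The primary outcome, session-by-session load monitoring, is collected only in the Pilates arm. A restricted set there limits generalisability but biases no between-arm contrast. Finally, a condensed article may leave follow-up of discontinued men to the full protocol, so its silence on their final evaluation is not itself a fault.

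All of this limits the consequence. It does not remove the conflict: the article states both rules, and they disagree.

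**Conclusion.** The point stands as an unresolved contradiction with a conditional consequence. If the exclusions govern, the secondary between-group comparisons are selected in one arm and tend to favour Pilates when poor attenders do worse. If they do no worse, no bias arises. On the assumptions shown, the shift is about 1.7 ms of rMSSD at 14.5% excluded, small against 19.02 ms, and larger only if exclusions are many or adherence is strongly tied to outcome. If intention to treat governs, men who could have been measured may receive the worst value in one arm only, which may bias against Pilates. The direction of bias therefore depends on which sentence is followed. Until that is settled, the intention-to-treat strength claimed in the Discussion cannot be relied on. The contradiction itself rests on no assumption about attendance.

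**What to change.** 1. State that all 54 randomised men are analysed as allocated in the between-group comparisons, using each man's recorded final evaluation whatever his attendance, progression or training injury. Obtain that evaluation where still possible. Trial status reports data collection in June 2019, so the remedy will rest mainly on keeping data already recorded.
2. Move all three training-linked criteria from study exclusions to the definition of a labelled secondary per-protocol set (31 or more of 36 sessions for attendance) or of the load-monitoring analysis. Moving attendance alone would leave the progression and injury rules in conflict with intention to treat. This concerns who is analysed, not whether a man continues training.
3. Restore the recorded data of anyone already excluded under these criteria, and report attendance and exclusions by arm.

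The cost is a few sentences, with no new participants and no procedure beyond the final evaluation already scheduled. The analysis is still described in the future tense, so the population can be settled before it is run. The small downside is that the intention-to-treat estimate may be smaller than one from adherers only.

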### Primary outcome

Quantification of the internal training load was evaluated in each training session with the three monitoring tools: SPE [6], HR [18], and HRV [18]. For the monitoring to be considered successful, two of the three monitoring tools must yield significant results. In addition, the correlation between SPE and HR should be moderate to high so that they can be used in clinical practice as low cost and easily applicable tools.

The SPE consists of a scale proposed by Borg where the participants choose the descriptor and number that best represents their psychophysiological stress in the training session [6]. It is a scale from 6 to 20 points, where 6 means “no effort” and 20 means “maximum effort.” To avoid biased responses, the question was standardized as: “From 6 to 20 points, how do you rate your perception of effort now?” All responses were recorded in individual records. The participants had previously been made familiar with the scale [6].

Prior to the sessions, participants were told how to estimate their SPE. It was explained to them that during the exercises it was necessary to perceive how much effort they were using so that every 5 minutes during a session they could estimate the SPE according to their individual perception for how exhausting the exercises were.

In addition, 15 min after the end of each session, the participants estimated the SPE again [6]. This final SPE was multiplied by the duration of the session in minutes, and the product represents the internal load in arbitrary units. The intensity of the session was classified into three zones according to the Borg scale used by Moreira et al. [19].

Quantification of the internal load training using the HR was performed using the TRIMP method. This evaluates the volume and intensity of the session through specific scores in each training zone, as proposed by Edwards [18, 20].

In addition to these methods for monitoring the training load, HRV was analyzed. The weekly mean of rMSSD (rMSSDmean) expressed in milliseconds and the weekly intra-individual coefficient of variation of rMSSD (rMSSDcv) expressed as a percentage will be used [21, 22]. These indices will be transformed to logarithms to mitigate outliers and simplify the analysis.

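### Men who fail to progress are excluded after randomisation, in effect only from the Pilates arm, which contradicts the stated intention-to-treat analysis and, if applied, conditions the results on response to training

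*Protocol article*

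**What the plan says.** Under Study design, Pilates "participants were required to pass through the three levels of the Pilates method: basic, intermediate, and advanced" over 36 sessions. Under Participants, several groups are removed in one sentence: men injured during training, "those who attended less than 85% of training sessions", "those who failed to progress between the three levels of the Pilates method", men who could not use the subjective scales, and "those with errors in the captured RR intervals were excluded from the study".

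The load data come from one arm only, since "The control group underwent only the initial and final evaluations, like the Pilates group" (end of Study outline). Background states the aim: "It is hypothesized that the protocol proposed by the study can be prescribed clinically". Under Primary outcome, "For the monitoring to be considered successful, two of the three monitoring tools must yield significant results", and the SPE–HR correlation should also be moderate to high. Under Statistical analysis, "The cutoff points for load increments with the HRV indices and SPE were obtained from the receiver operating characteristic curve", with sensitivity, specificity and predictive values for each level.

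The same section ends by placing all men from the initial assessment under intention to treat, with the worst outcome seen in the study group as the chosen value. The Discussion names intention to treat as a strength.

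**The concern.** Failure to progress cannot be an eligibility criterion. It is a response to the assigned programme, seen during training, and a control man cannot meet it. Removing men for it breaks the randomised comparison on one side only. It also selects on the process that the trial sets out to describe, namely how internal load behaves as men move from basic to advanced and at what value load is increased.

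Three things are at stake:

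- The arm comparison would set all controls against Pilates men who responded well enough to advance.
- The load curves, the correlation and the per-level cut-offs would describe men who completed the progression.
- The share of men who could complete it bears directly on whether the programme can be prescribed, yet among the analysed men it would be 100% whatever the true share.

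**Working it through.** **1. The two rules side by side.** Participants removes non-progressors from the study. Statistical analysis keeps everyone from the initial assessment. Both cannot hold, and the article does not say which governs the load and ROC analyses. The worst-outcome rule does not settle it. A worst value is not defined for a session load, a weekly ln rMSSD, a correlation or a ROC cut-off, and a substituted value would replace sessions that were actually recorded.

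**2. The plan's own figure.** Inputs from Sample size calculation: difference 19.02 ms, SD 23.94 ms, two-sided 5%, power 80%.

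n per group = 2 × (1.960 + 0.842)² × (23.94/19.02)² = 24.87, so 25, as stated. Then 25 × 1.1 = 27.5, given as 27. Keeping all 27 Pilates men changes nothing here.

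**3. Between-arm comparison if men are removed.** The number of non-progressors is not given. I assume a share f of the 27 is removed, being those lowest on a latent coping score that correlates r with the outcome (r from 0.2 to 0.5). With φ the normal density and z_f its f-quantile, the Pilates mean shifts by r × h(f) SD, where h(f) = φ(z_f)/(1 − f).

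| f | Pilates men left | h(f) | Shift, SD | Shift, ms (× 23.94) | Power for 19.02 ms (t test, 27 controls) | Rejection rate with no true effect |
|---|---|---|---|---|---|---|
| 5% | 26 | 0.109 | 0.02–0.05 | 0.5–1.3 | 81% | 5.1–5.4% |
| 10% | 24 | 0.195 | 0.04–0.10 | 0.9–2.3 | 79% | 5.2–6.3% |
| 20% | 22 | 0.350 | 0.07–0.17 | 1.7–4.2 | 77% | 5.7–9.2% |
| 30% | 19 | 0.497 | 0.10–0.25 | 2.4–5.9 | 74% | 6.2–12.8% |

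The loss of power is modest. Selection is the main problem.

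**4. Load cut-off, illustration only.** Assume normal loads with SD 1 at two adjacent levels, within-man correlation 0.7, a true step of 1 SD, and removal of the share f with the highest next-level load. Take the midpoint of the two level means as a stand-in for the ROC cut-off.

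- The next-level mean falls by h and the lower-level mean by 0.7h, so the midpoint falls by 0.85h: 0.17, 0.30 and 0.42 SD for f = 10%, 20% and 30%.
- If failure correlates only 0.5 with load, these halve to about 0.08, 0.15 and 0.21 SD.
- The plan's smallest worthwhile change for SPE is 0.2 between-subject SD.
- The step among retained men is 1 − 0.3h: 0.94, 0.90 and 0.85.

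**5. Does keeping the men repair the level comparison?** Not by itself. Suppose non-progressors have no next-level sessions.

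- Pooling all men at the lower level with the remaining men at the next gives a step of 1 − h: 0.81, 0.65 and 0.50. That is worse than exclusion.
- Comparing each man only with himself gives 0.94, 0.90 and 0.85 again.
- A random-effect model with one load per man per level falls between. Its step is (1 − h) + s × 0.7h, where s is the slope of next-level on lower-level load among retained men (0.58, 0.51, 0.46). That gives about 0.88, 0.78 and 0.66.

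No method recovers the true 1.00 when the men who failed have no data at the next level.

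**The case against.** The intention-to-treat sentence is in the plan, so it cannot be taken as settled that the analyses use only men who progressed. This stands: the defect is an unresolved contradiction.

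A reader might infer that the trial succeeds by construction. The documents do not support that. Success means two of three tools significant plus a moderate to high correlation, and the share progressing is not a declared outcome. In the model above, selection shrinks the step between levels, so it does not manufacture a positive result. What is fixed by definition is only the share progressing among analysed men.

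A reader might also infer that the cut-offs are set too low because the men with the highest load are gone. The article gives no reason for failure, which could reflect technique or interrupted training. The cut-offs also cover HRV indices, for which the direction could reverse if they fall as load rises. Reporting accuracy for each level suits discrimination between levels; the text does not speak of tolerated and untolerated increments. The midpoint is not a ROC cut-off.

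Finally, Trial status reports 54 randomised and no exclusion after randomisation, and failure shares of 20–30% would exceed the plan's whole 10% withdrawal allowance. The effect may be small or nil. The rule is still written into the plan and needs resolving before analysis.

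**Conclusion.** The point holds as a contradiction with consequences. One section removes men on a post-randomisation response that only the Pilates arm can show; another promises intention to treat, and its substitution rule is unworkable for session-level data. If the exclusion governs, the arm comparison and the load, correlation and ROC analyses are conditioned on response to training.

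The size and direction of the bias cannot be determined from the documents. The between-arm shifts (0.02–0.25 SD) rest on assumed failure shares of 5–30% and an assumed link between coping and outcome. The SPE cut-off shifts (roughly 0.1–0.4 SD) rest on shares of 10–30% and on non-progressors carrying higher load. Neither is an estimate for this trial.

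**What to change.** Reconcile Participants with Statistical analysis as follows:

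- Remove failure to progress as a ground for exclusion from analysis. This concerns who is analysed and changes no training rule.
- Keep every randomised man in the between-arm comparison.
- In the load, correlation and ROC analyses, use all sessions actually attended, with observed data and no worst-value substitution.
- Compare levels within man, for example with a mixed model with a random man effect, and show the purely within-man contrast beside it. Do not pool different men at different levels. State that men with no sessions at a level cannot inform that step.
- Report the number and proportion of Pilates men reaching each level, with exact 95% CI.
- Label any completers-only analysis as a sensitivity analysis.

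The cost is a few sentences and one small table. Data are recorded session by session, and most of the analyses are still described in the future tense. The downsides are unequal numbers per level, a slightly more complex model, and a progression figure that may look less favourable.
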